# Using electroacupuncture to recover muscle strength in patients with knee osteoarthritis after total knee arthroplasty: a study protocol for a double-blinded, randomized, and placebo-controlled trial

**DOI:** 10.1186/s13063-020-04601-x

**Published:** 2020-08-10

**Keywords:** Electroacupuncture, Knee osteoarthritis, Total knee arthroplasty, Study protocol

## Abstract

**Background:**

Total knee arthroplasty (TKA) is a gold standard for patients with terminal term gonarthrosis for reducing pain, correcting deformities, and regaining stability. However, post-TKA muscle strength recovery is often difficult. Although electroacupuncture (EA) enhances lower extremity muscle strength of the lower extremity, there is limited evidence regarding its effect on lower extremity muscle strength in post-TKA patients. Consequently, this trial intends to evaluate the efficacy of post-TKA EA on the recovery of lower extremity muscle strength, specifically, during the early post-TKA period.

**Methods/design:**

This is a double-blinded, randomized, and controlled trial. It will be conducted between August 2020 and December 2020. Ninety-four participants with KOA who have undergone unilateral TKA will be randomized into a treatment (EA) group and a control (sham EA) group. The former and latter groups will receive EA and sham EA, respectively, at ST37, ST36, SP10, and SP9 acupoints. The participants will undergo ten treatment sessions over 2 weeks (5 sessions per week). The primary outcomes will include changes in muscle strength and the Hospital for Special Surgery score at the second week from baseline (pre-op 1 day or POD 3). The secondary outcomes will include a 4-m walk test, numerical rating scale score, the Hamilton Anxiety Scale score, and additional analgesia use. Additional outcomes will include the incidence of analgesia-related side effects and the participant satisfaction rate. Participant blinding will also be assessed where they will be asked to guess whether they received EA after the latest intervention. Adverse EA events will be documented and assessed throughout the trial.

**Discussion:**

EA is helpful for post-TKA recovery and enhancement of lower limb muscle strength.

**Trial registration:**

Chinese Clinical Trial Registry ChiCTR1900027806. Registered on 29 November 2019

## Background

As a common chronic joint disease in orthopaedics, knee osteoarthritis (KOA) is mainly aetiologically caused by degenerative changes in the articular cartilage and the resulting hyperosteogeny. This results in complications, including knee pain, stiffness, and dysfunction. Given the improvements resulting from new biomaterials and surgical techniques, total knee arthroplasty (TKA) is now a first-choice treatment for patients with severe KOA for improving their quality of life [1, 2]. Compared with non-surgical treatment, TKA significantly relieves pain and promotes functional improvement in patients with severe KOA [3]. More than 700,000 TKA procedures are performed annually in the USA to relieve KOA-related pains and disability, which is expected to reach 3.5 million per year by 2030 [4]. Despite the objective post-TKA improvements in knee function and its imaging parameters, 19–23% of post-TKA patients still report dissatisfaction at the 6-month follow-up [5, 6]. Compared with healthy adults, there are post-TKA deficits in lower limb muscle strength, which reduces walking distance and stair climbing speed [7, 8]. Lack of muscle strength increases the risk of falling, which makes the patients lose their independence. Muscle strength rehabilitation of the knee extensor and flexor is essential for functional improvement of patients with KOA since knee stability is primarily supported by the soft tissue of the quadriceps femoris and hamstring. A post-TKA decrease in the strength of the quadriceps femoris and hamstring [9–12], which is associated with decreased function [13, 14], has been reported. Moreover, there have been reports of difficulty with post-TKA muscle strength recovery. For example, surgical incision pain reduces the patient’s ability to exercise. In the first post-TKA month, the strength of the quadriceps femoris decreased by 60% [15]. Although the strength of the quadriceps improves over time, approximately 30% of post-TKA patients have reported deficits at > 2 postoperative years compared with healthy adults [16]. Immediately after the operation, the hamstring strength has been reported to reduce by 50% [11, 17]. Previous studies have reported TKA-related weakness and gait biomechanical damage to the quadriceps femoris and hamstring that may last for several years [18, 19]. Standardized physiotherapy is beneficial towards muscle functional improvement [20]. Moreover, neuroregulatory techniques, including neuromuscular electrical stimulation and electroacupuncture (EA), have become increasingly popular as post-TKA rehabilitation therapy [21]. Effective post-TKA neuroregulatory techniques can enhance lower limb muscle strength, which fast-tracks rehabilitation and reduces the financial burden of patients [22].

EA is primarily recommended for pain modulation and has been shown to enhance muscle strength [23, 24]. However, there have been few randomized controlled trials on post-TKA patients with limited evidence regarding the EA effect on lower limb muscle strength. Therefore, we designed a double-blinded, randomized, and placebo-controlled trial to investigate the EA effects on lower limb muscle strength in post-TKA patients, specifically, during the early postoperative period.

### Objectives

To evaluate the efficacy of EA after TKA for enhancing the muscle strength of the lower extremity in the early postoperative period.

## Methods/design

This trial will be conducted at the Department of Joint Orthopaedics, Shanghai Guanghua Hospital of Integrated Traditional Chinese and Western Medicine, Shanghai, China, which is a teaching and tertiary hospital of Shanghai University of Traditional Chinese Medicine, Shanghai, China. Patients with KOA who will undergo unilateral TKA will be mainly enrolled from the orthopaedics wards of Shanghai Guanghua Hospital of Integrated Traditional Chinese and Western Medicine, Shanghai, China, through advertisements. We followed the SPIRIT 2013 Statement [25] and STRICTA [26] to report this trial protocol. This study has been approved by the ethics committee of Shanghai Guanghua Hospital of Integrated Traditional Chinese and Western Medicine (Ethics Approval Number: 2019-K-23) and registered at the Chinese Clinical Trial Registry. All participants will be asked to provide written informed consent and will be informed that the trial will not involve the collection of biological specimens for storage.

### Eligibility criteria

The inclusion criteria will be as follows: (1) 60–80 years of age, (2) diagnosed with KOA and willing to undergo unilateral TKA, (3) undergone similar surgical approach with normal blood coagulation function, (4) having posterior cruciate-stabilizing prostheses (Smith & Nephew, London, UK), (5) having well-placed knee prosthesis (as shown by the postoperative X-ray), and (6) postoperative clear consciousness and normal cognitive function.

The exclusion criteria will be as follows: (1) serious nervous system problems, cardiovascular diseases, osteoporosis, and metabolic diseases; (2) having coagulation disorder, haemophilia, or tumour; (3) intraoperative bone fracture, dislocation, and structural abnormality; and (4) skin damage in the acupoint area.

### Exit criteria and management

Exit criteria include (1) participant request, (2) severe postoperative complications (e.g. pulmonary embolism), and (3) intratreatment side effects.

### Sample size

The sample size will be calculated using the previously reported peak torque (PT) of the quadriceps femoris [27]. The formula is as follows:
$$ n=\frac{2{\left({Z}_{\alpha }+{Z}_{1-\beta}\right)}^2{\sigma}^2}{\Delta ^2} $$

An effect size (△) of 2 with a standard deviation (SD) of 3.34 between EA and RT (*n* = 33*2/0.85 = 82) will be adopted. Based on this data, a two-group trial will be conducted with 39 participants per group, *α* = 0.05 (two-sided), and *β* = 0.2 (80% power) [28]. With a possible sample loss of 15%, the final sample size will be set to 47 participants per group.

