#### Basic physical therapy

Both groups will undergo basic post-surgery physical therapy (exercise) from 24 h after TKA. The programme will be supervised by a physical therapist and involve ankle pumping exercises, hip flexion (straight leg raise), and pain-free knee mobilization in flexo-extension. The exercises will be performed daily at 30-min sessions for 2 weeks. Additionally, the participants performed ankle pumping exercises with the lower extremities elevated and respiratory exercises for the first 24–48 post-TKA hours.

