## Discussion

EA is an improvement of the traditional manual acupuncture method that involves modern electronic equipment to enhance the intensity of mechanical acupuncture stimulation for its beneficial effects, including pain relief, muscle relaxation, and circulation improvement [40, 41]. EA is effective in improving muscle strength and promoting functional rehabilitation [42, 43]. To our knowledge, the EA treatment effects on post-TKA muscle strength improvement remain to be validated by randomized and placebo-controlled trials. Consequently, this trial will aim to examine EA efficacy in improving muscle strength during the early post-TKA period compared with the sham EA. This is to provide evidence regarding clinical EA application for patients with KOA after unilateral TKA. To maximize the exclusion of placebo effects, a rigorous and methodological design will be followed, including non-acupoints, non-penetrating acupuncture, and special electrode wires with electricity output for control. Further, the participants will separately receive treatments at different times to avoid inter-participant communication and interference. The aforementioned methods will likely allow successful participant blinding and objective evaluation of the EA efficacy for post-TKA patients.

Given its decent analgesic effects, EA can reduce the post-TKA use of opioids and non-steroidal anti-inflammatory drugs. In the past several years, there has been a worldwide increase in the support for ERAS given its contribution to pain relief and functional recovery [44]. Early post-TKA EA treatment could eventually become an important component of ERAS. We believe that this trial will contribute to enhancing lower limb muscle strength after TKA, and thus provide evidence for primary TKA rehabilitation.

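### The planning difference and SD are labelled EA versus an undefined RT, are used without justification for EA versus sham EA, and do not give the stated 80% power at 39 to 40 evaluable per group

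*Protocol article*

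**What the plan says.** The Sample size section names the outcome and its origin: "The sample size will be calculated using the previously reported peak torque (PT) of the quadriceps femoris". It then gives the planning inputs: "An effect size (△) of 2 with a standard deviation (SD) of 3.34 between EA and RT". Alpha is 0.05 two-sided and power is 80%. The size follows: "a two-group trial will be conducted with 39 participants per group", and then "With a possible sample loss of 15%, the final sample size will be set to 47 participants per group".

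The comparison that the trial makes is given in the Abstract, where participants "will be randomized into a treatment (EA) group and a control (sham EA) group". Randomization and blinding, the Sham EA group section and the Discussion all describe the same two arms. Exercise is common to both: "Both groups will undergo basic post-surgery physical therapy (exercise) from 24 h after TKA". RT occurs only in the Sample size section and is absent from the Abbreviations list. On existing evidence, the Discussion states that "EA treatment effects on post-TKA muscle strength improvement remain to be validated by randomized and placebo-controlled trials".

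**The concern.** The planning difference is labelled with one contrast and used for another. The article does not say that RT means sham EA, and it gives no reason why a difference of 2 should apply to a sham-controlled comparison. A reader therefore cannot tell what the power statement assumes about EA versus sham EA, which is the trial's question.

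The choice of comparator can matter for this outcome. Peak torque is measured at maximum voluntary effort, and the Discussion says the sham is meant to exclude placebo effects as far as possible. A difference measured against some other control need not equal the difference against sham.

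The power figure is what gives a non-significant result its weight. If the assumed difference has no stated link to the sham contrast, and the 80% is not reached even at that difference, such a result could be taken as stronger evidence against EA than the design supports.

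**Working it through.** **1. The contrasts side by side**

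| Item | Sample size section | Rest of the article |
|---|---|---|
| Active arm | EA | EA |
| Comparator | RT, undefined | Sham EA: non-penetrating needle, no current |
| Exercise | Not stated for the source | Same programme in both arms |
| Reason for using 2 against sham | None given | None given |

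The mismatch is visible in the text itself and needs no outside source. What RT was does need one.

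**2. The plan's own figure**

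Inputs, all from the Sample size section: Δ = 2, σ = 3.34, two-sided α = 0.05, power 80%, and 39 per group before 15% loss. The article's formula is n = 2(Z_α + Z_{1−β})²σ²/Δ².

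- Two-sided: 2 × (1.960 + 0.842)² × 3.34² / 2² = 43.8, so 44 per group. By t test, 44 gives 79.3% and 45 gives 80.2%.
- One-sided, for comparison: 34.5, so 35 per group.
- Neither version gives the stated 39.

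The figures in the article's bracket do not lead to 39 as a pre-loss size either: 33 × 2 / 0.85 = 77.6, not 82. Since 33 / 0.85 = 38.8, the 39 may already contain the loss allowance, but the text does not settle this.

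**3. Evaluable patients under the plan**

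47 × (1 − 0.15) = 39.95, so about 40 per group. With the stated 39, the relevant range is 39 to 40.

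**4. Power and detectable difference**

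Two-sample t test, noncentral t, with noncentrality Δ / (σ√(2/n)) and 2n − 2 degrees of freedom. For n = 39 and Δ = 2: 3.34 × √(2/39) = 0.756, and 2 / 0.756 = 2.64, which gives power of 74.2%. The normal approximation gives 75.3%.

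| True EA–sham difference | 39 per group | 40 per group | 47 per group (no loss) |
|---|---|---|---|
| 2.0 | 74% | 75% | 82% |
| 1.8 | 65% | 66% | 73% |
| 1.6 | 55% | 56% | 63% |
| 1.5 | 50% | 51% | 58% |
| Detectable at 80% power | 2.15 | 2.12 | 1.95 |

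The first row and the last use only the plan's inputs. The rows at 1.8, 1.6 and 1.5 are hypothetical: they assume that the SD stays at 3.34 and that the true difference from sham is 10%, 20% or 25% below 2. The document supports no particular value. A true difference above about 2.15 would give more than 80% power.

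**The case against.** The strongest reply is that power is conditional on the difference adopted. Once the article adopts 2 for this two-group trial, the power statement concerns this trial under that assumption, wherever the number came from. Borrowing from the nearest available comparison is ordinary practice when no sham-controlled estimate is known, and a journal article may leave the rationale to the full protocol. This stands in part. It rules out saying that the 80% simply belongs to another trial's contrast. It does not cover the positive labelling of the inputs with an undefined comparator, and it does not rescue the 80%, which fails at a difference of 2.

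A reader might go further and infer that RT was an arm without sham, that 2 therefore contains expectation and attention effects, and that the trial is known to be underpowered against sham for that reason. The document does not support this. RT could be a leftover label for the control, routine therapy with or without a sham, or an active training arm. If it was an active treatment, the difference from sham could exceed 2. The Discussion's remark about missing placebo-controlled evidence does not describe the arms of the cited source. The direction of any error is open.

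It is also fair to say that the fall from 80% to 74–75% is an arithmetic shortfall that would exist whatever the comparator. It is reported here because correcting the label alone would leave a wrong power figure in the same paragraph.

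**Conclusion.** The point holds in limited form. The planning difference of 2 and SD of 3.34 carry the label EA versus RT, RT is undefined, and nothing justifies their use for EA versus sham EA. Whether 2 is too large or too small for the sham comparison cannot be determined.

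With these inputs, two-sided alpha 0.05 and 39 to 40 evaluable per group, power is about 74 to 75% by t test rather than 80%. It reaches 82% only if all 47 per group are evaluable. These figures assume a two-sample t test, an SD of 3.34 in both arms and 15% loss as planned. Power below 74% depends on a true EA–sham difference smaller than 2, which is a hypothesis and not a finding.

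**What to change.** In the Sample size section:

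- Define RT and state which contrast and source population the difference of 2 and the SD of 3.34 come from.
- Give the unit of the difference, as in the source measure.
- Justify the difference for EA versus sham EA, for example as the smallest such difference worth detecting.
- Keep 47 per group, but replace the 80% claim with about 74 to 75% power at a difference of 2 with 39 to 40 evaluable per group, or equivalently with a detectable EA–sham difference of about 2.12 to 2.15 at 80% power.
- Add power at 1.8 (65–66%), 1.6 (55–56%) and 1.5 (50–51%), labelled as a hypothetical sensitivity range.
- State that a non-significant result will be read from the confidence interval against the justified difference.

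The cost is rewording one paragraph and accepting a less favourable power figure, with no extra patients or procedures. The limit is that rewording discloses the position and does not raise power. If the justified EA–sham difference turned out to be below about 2.1, reaching 80% would need more participants: by the article's formula, 55 per group at 1.8, or 65 after 15% loss.

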### Recruitment strategies and enrollment

Participant registration will be conducted between August 2020 and December 2020. Written informed consent will be obtained from all participants for inclusion in any other scientific publications. When the participants are hospitalized, a trained nurse and several physiotherapists will implement the enhanced recovery after surgery (ERAS) pathway (Fig. 1). Figure 2 presents the trial flow, which includes participant recruitment, eligibility screening, randomization, intervention, and outcome assessments. Figure 3 presents an overview of the trial design, conduct, review, and analysis. A filled-out SPIRIT 2013 checklist (Word) is presented in Additional file 1.

**Fig. 1 Fig1:**
[figure not shown]
Enhanced recovery after surgery pathways

**Fig. 2 Fig2:**
[figure not shown]
The trial flow diagram

**Fig. 3 Fig3:**
[figure not shown]
The schedule of trial enrollment, interventions, and assessments

### Randomization and blinding

Independent research staff will use RV.3.5.1 software to generate a randomly numbered sequence for complete random grouping. A number sequence will be sealed by an independent assistant in an opaque envelope containing treatment information. Eligible and consenting patients with KOA who have undergone unilateral TKA will be randomly assigned to the EA and sham EA groups at a ratio of 1:1 (each group, *n* = 47). Only the physiotherapist in charge of EA treatment is authorized to open the envelope and enrol participants.

All the participants, physiotherapists, outcome assessors, and data statisticians will be subject to blinding. To help maximize participant blinding, a pragmatic placebo needle will be employed and a sham EA design will be applied. Unblinding before study completion will only be allowed in the case of medical emergencies or severe adverse events.

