#### EA group

Based on the new standard of “International Acupuncture Nomenclature” [29], the LIANGQIU (Stomach 37, ST37), ZUSANLI (Stomach 36, ST36), XUEHAI (Spleen 10, SP10), and YINLINGQUAN (Spleen 9, SP9) acupoints on the surgery side will be employed (Fig. 4). After skin disinfection, adhesive pads (size 8 × 10 mm, Suzhou Medical Supplies Factory, Suzhou, China) will be placed on the acupoints through which acupuncture needles (size 0.25 × 40 mm, Suzhou Medical Supplies Factory, Suzhou, China) will be inserted approximately 3 cm into the skin (Fig. 4). After achieving de qi sensation, the acupuncture points will be stimulated using Huatuo SDZ-II EA apparatus (Suzhou Medical Supplies Factory, Suzhou, China). The intensity of the constant current square wave pulse at a frequency of 40 Hz and a pulse width of 1 ms will be gradually increased until it reached an intolerable intensity. The treatment of the EA group will involve ten 30-min sessions over 2 weeks (5 sessions per week).

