#### Sham EA group

In the sham EA group, sham EA using a pragmatic placebo needle [30] (size 0.25 × 30 mm) will be applied on sham acupoints for 5 sessions per week. Each sham acupoint will be at 1 cun (≈ 20 mm) lateral to the acupoints (Fig. 5). The pragmatic blunt-tipped placebo needle will be inserted into the adhesive pads without skin penetration (Fig. 4). A Huatuo SDZ-II EA apparatus (Suzhou Medical Supplies Factory, Suzhou, China) will be connected to the sham acupoints through special electrode wires without electricity output. The sham needles will remain in the adhesive pads for 30 min in each session. The sham EA and EA treatment processes are similar except the former does not involve skin penetration, needle manipulation, and electric output.

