#### Muscle strength

Knee muscle strength will be evaluated as the PT of knee flexion and extension using Biodex 4 isokinetic muscle strength tester (IST, Biodex Medical Systems, New York, USA). Before the test, the physiotherapist will stabilize the participant on a dynamometric chair in a 90° sitting position with the torso and thighs fixed. The machine’s power axis will be aligned with the knee rotation centre. Moreover, the participant will be asked to move the knee to measure the range of motion within those of previous tests. The physiotherapist will set the angular velocity at 60°/s and ask the participant to perform five constant flexion and extension activities. During the test, the participant will use his/her maximum strength in each flexion and extension activity to measure the PT of knee flexion and extension. The test will be independently conducted by the physiotherapist.

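### The blinded list includes every physiotherapist, which cannot be true of the one who delivers EA or sham EA, and the strength test is not clearly assigned to a blinded assessor

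*Protocol article*

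**What the plan says.** Four parts of the protocol article bear on this.

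- **Randomization and blinding** lists who is blinded: "All the participants, physiotherapists, outcome assessors, and data statisticians will be subject to blinding". No physiotherapist is excepted. The same section says of the allocation: "Only the physiotherapist in charge of EA treatment is authorized to open the envelope and enrol participants". The sequence is "sealed by an independent assistant in an opaque envelope containing treatment information".
- **EA group** and **Sham EA group** describe delivery. In the active arm the needle enters the skin by about 3 cm, and "After achieving de qi sensation, the acupuncture points will be stimulated using Huatuo SDZ-II EA apparatus". For the comparison of arms, "The sham EA and EA treatment processes are similar except the former does not involve skin penetration, needle manipulation, and electric output".
- **Outcome evaluations** names two primary outcomes, muscle strength and the HSS score. Strength is measured before surgery and 2 weeks after the intervention.
- **Muscle strength** has the physiotherapist position the participant, set the dynamometer and ask for five repetitions at full effort. It ends: "The test will be independently conducted by the physiotherapist".

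**The concern.** The blinding statement covers a person who, by the same section, learns the allocation. A trial report that repeated it would describe more blinding than the design can deliver.

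The second part concerns a primary outcome. The machine reads peak torque, but the value depends on how hard the participant tries, and so on how the tester sets up, instructs and encourages. A tester who knows the arm could produce a between-arm difference without intending to. The analysis could not remove that difference afterwards. The planned blinding questionnaire would not reveal it either, because it asks participants only. The document should therefore make clear that the tester is blinded. The only sentence that could do so is the general blinding statement, and that statement is already wrong for one physiotherapist.

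**Working it through.** The finding rests on comparing passages. The arithmetic at the end is only an illustration.

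**Step 1. Can the treating physiotherapist be blinded?**
- The envelope holds the treatment, and the physiotherapist in charge of EA opens it (Randomization and blinding).
- Delivery would reveal the arm even without the envelope. One arm has skin penetration, de qi and rising current. The other has a blunt needle held in the pad, no manipulation and no output (EA group, Sham EA group).
- Each fact alone rules out blinding of that person. The inclusion of physiotherapists without exception is therefore contradicted by the document's own text.

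**Step 2. Is the strength tester identified as blinded?**
- The blinded list names outcome assessors and physiotherapists as separate groups.
- The Muscle strength section uses the physiotherapist label, not the assessor label. It says neither that the tester is an assessor nor that the tester is someone other than the treating physiotherapist.
- The closing word, independently, may mean apart from treatment or simply unaided. The text does not settle which.
- Result: separation is possible but not stated.

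**Step 3. Which measurements are exposed?**
- Randomization is of patients who have already had their TKA, and the first strength test is before surgery. That test precedes allocation and cannot be affected by knowledge of it.
- Only the 2-week strength test is exposed. The argument does not extend to the HSS score.

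**Step 4. Hypothetical size.** The document gives no figure for a tester effect, so none can be reproduced. To show how sensitive the test would be:
- SD = 3.34 and 15% loss (Sample size). 47 × 0.85 = 39.95, so about 40 per arm.
- Standard error of the difference = 3.34 × √(2/40) = 0.747.
- Noncentrality = bias / 0.747. The rejection probability comes from the noncentral t with 78 degrees of freedom, two-sided critical value 1.991, and a true EA effect of zero.

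| Assumed tester-induced difference | Noncentrality | False-positive rate |
|---|---|---|
| 0 | 0 | 5.0% |
| 0.25 | 0.335 | 6.3% |
| 0.5 (a quarter of the planned 2) | 0.669 | 10.1% |
| 1.0 (half of the planned 2) | 1.339 | 26.2% |

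The first column is assumed. The Sample size section gives no unit for the 2 and the 3.34, and the SD there comes from a comparison of EA with RT. The table shows what a bias of a given size would do, not what bias to expect.

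**The case against.** The strongest reply accepts Step 1 and contests Step 2. The protocol singles out one physiotherapist as being in charge of EA. Once that person is excepted, the blinding sentence can be read as covering all the others, including a tester. Outcome assessors are listed as blinded, and under Data management and monitoring they alone have access to the case report forms, which suggests that assessors record the strength result. The test is described as independent. Under Recruitment strategies and enrollment, "a trained nurse and several physiotherapists will implement the enhanced recovery after surgery (ERAS) pathway", so there is more than one physiotherapist. The dynamometer, at a fixed speed with torso and thighs restrained, also limits subjectivity in scoring.

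Much of this stands. It makes a separate, blinded tester plausible, and it defeats the stronger reading a reader might take, that the person who needles the patient will also measure strength. The document does not say so. It does not secure separation, however. The sentence on several physiotherapists concerns the ERAS pathway, sole access to the forms governs recording rather than conduct of the test, and a fixed machine does not control effort or encouragement.

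A reader might also infer that the daily exercise is supervised by the unblinded physiotherapist, because under Basic physical therapy "The programme will be supervised by a physical therapist". Nothing links that person to the one in charge of EA, and who supervises which session is staffing detail that an article may leave to the full protocol. No point is made of it here.

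**Conclusion.** The blinding statement is wrong as written for the physiotherapist who delivers EA or sham EA. This follows from the document alone and needs no assumption.

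The blinding of the strength test is unsecured, not shown to be broken. The exposure is limited to one of the two primary outcomes and, within it, to the 2-week test. How much it matters depends on whether the tester is in fact separate and on how far a tester can move maximal effort. The document answers neither question.

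The rates of about 10% and 26% rest on assumed tester effects of 0.5 and 1.0 units, with SD 3.34 and 40 per arm. A reader might take them as this trial's error rate, but the document gives no evidence for a bias of any size.

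**What to change.** 1. **Randomization and blinding:** state that the physiotherapist who delivers EA or sham EA is not blinded, and take that role off the blinded list.
2. **Muscle strength:** state that the test is run by one of the blinded outcome assessors already named under Randomization and blinding, who delivers no EA or sham EA and has no access to the envelopes.

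No change to outcomes, sample size or treatment is needed. The cost is wording and a duty roster, with somewhat less rota flexibility and a less favourable blinding statement. The document does not show that the existing assessors can operate the dynamometer, so the sponsor should confirm this.
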